# **Protocol Title: A Prosthetic Foot Test-Drive Strategy for Improving Stability and Falls-Related Outcomes in Veterans with Leg Amputations**

## **1.0 Objectives**

### ***Specific Aim 1: Determine the effects of commercial prosthetic feet of varying stiffness on stability and falls-related outcomes in Veterans with TTA***

*H1.1:* Prosthetic feet with the lowest coronal plane stiffness will correlate with greater self-reported (i.e., Perceived Stability) and biomechanical (i.e., Medial/Lateral Margin of Stability (MOS)) stability outcomes during walking on uneven ground and cross-slopes, as well as greater balance confidence (i.e., ABC), performance-based stability (i.e., NBWT and Four Square Step Test (FSST)), and less activity restriction (i.e., PROMIS Ability to Participate in Social Roles and Activities (APSRA)) after community use.

*H1.2:* Prosthetic feet with the lowest sagittal plane stiffness will correlate with greater self-reported (i.e., Perceived Stability) and biomechanical (i.e., Anterior/Posterior MOS) stability outcomes during walking on inclines, as well as greater balance confidence (i.e., ABC) and stability (i.e., NBWT and FSST), and less activity restriction (i.e., PROMIS APSRA) after community use.

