### Visits 4, 5 and 6: Follow-up Testing Visits (up to 4 hours each)

During each of these visits, participants will be asked to complete a survey that includes questions about their preference, stability, perceived foot stiffness, satisfaction, balance, activity restrictions, fear of falling, and mobility while using the study assigned prosthetic foot that they wore for the past week. During each of these visits, participants will be asked to repeat some of the performance-based balance-related outcome measures (i.e., FSST, 4SBT, NBWT, L test) (as described under Visit 1, with the only difference being that participants will be wearing the respective study prosthetic foot during visits 4, 5, and 6).

Furthermore, during these visits, a 16-camera motion capture system (Vicon Motion Systems Ltd., Oxford, UK) or an IMU system (XSens, Movella Inc., Henderson, NV, USA) may be used to collect positional data, using the same procedures described above in visits 2-3. Up to eighty reflective markers, or up to twenty-five IMUs, will be placed on anatomical locations (e.g., arms, legs, torso) and corresponding measurements will be taken (e.g., leg length, ankle width) according to the Vicon Full Body Plug-In Gait method. No data will be shared with Vicon Motion Systems Ltd. or Movella Inc. Participants may be asked to repeat some of the previous study procedures (i.e., walking conditions) while biomechanics data is being collected. Specifically, they may be asked to repeat

some of the previous study activities, including standing and walking trials overground and on the level, inclined, cross-slope, and uneven treadmill conditions (see details above, depending on their LM or HM group assignment) at their self-selected comfortable, slow, and fast walking speeds using the study foot that they have accommodated to following their one-week at home trial. As is standard for gait biomechanical data collection, the infrared motion capture cameras will collect marker coordinate data during walking if using the marker-based motion capture system. Embedded force platforms may also be used to collect synchronized ground reaction force data. The participants will be allowed to rest as much as needed between or during study activities.

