## **2.6 Data Analysis**

### Statistical Analysis

For both H1.1 and H1.2 (see Objectives section, 1.0 above for hypotheses details), linear mixed effects regression will be used to assess the association between Perceived Stability score, MOS, ABC, NBWT, or FSST (the dependent variables) and prosthetic foot (the independent fixed effect) with random effects for study participant. For H2.1 linear mixed effects regression will be used to test for correlation between Perceived Stability score for the emulated foot (the independent fixed effect) and follow-up Perceived Stability score for the corresponding actual foot (the dependent variable) with study participant as a random effect. For H2.2, similar models will be used to test for associations between the Perceived Stability score in the emulated foot (the independent fixed effect) and follow-up ABC, NBWT or FSST in the actual foot (the dependent variable). For H3.1 and H3.2, linear mixed effects regression will be carried out as above with initial Perceived Stability score as the independent fixed effect and Perceived Stability score, ABC, NBWT or FSST as the dependent variables with participant as the random effect. Linear mixed effects regression provides a more flexible approach to analyze repeated measures data compared to the traditional repeat measures models, with fewer model assumptions and the ability to incorporate data from participants who do not complete the study. These models account for non-independent data due to within-participant repeated measures by estimating separate between- and within-participant errors. For all models, mean and standard errors of the outcomes for each prosthetic foot and pair-wise mean differences and 95% confidence intervals (CI) across the three feet will be estimated and tested for significance.

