Power Analysis: Sample size for this study was based on pilot data collected in support of Specific Aim 1. Power analysis was carried out for two of the primary study variables: NBWT and MOS (H1.1 and H1.2). For NBWT we obtained overall mean, between and within participant variances based on pilot data for 45 participants testing for differences in NBWT using a multi-axial/split-toe foot (n=34) vs. a solid keel foot (n=11). Participants using the former foot walked a mean 3.4 ft farther than participants using the solid keel foot, with between and within participant standard deviation (SD) 4.1 and 2.7, respectively. Using these estimates, we simulated 5000 datasets of NBWT with sample size equal to 40 and 50 participants, each wearing all 3 feet (within-participant design), and with 1 mean pair-wise difference in NBWT of 2 ft; smaller differences than found in the pilot data as that study estimated between-participant differences which tend to be larger. For each dataset, linear mixed effects regression was carried out as described in the methods section, and power was estimated based on a type 1

error of .01, as we have 5 outcomes of interest. We estimate 81% and 91% power to detect differences in NBWT of 2 ft. for sample sizes of 40 and 50 respectively. Using estimates obtained from Gates et al (2013), we simulated MOS in participants with TTA walking on uneven surfaces, using 8.3 cm, 1.9 cm and 1.0 cm as the mean, between-participant and within-participant SDs respectively using a similar procedure as above. We estimate 98% power to estimate a pair-wise difference between prosthetic feet of 1 cm for 40 participants, and 87% power to estimate a difference of 0.7 cm for 50 participants. Considering the potential for attrition, we will recruit 60 participants (30 at each site), so that even if 20% of the recruited participants drop out (a conservative estimate based on the <5% drop out rate in our current emulator study with the same number of study sessions), we will still have enough participants for adequate statistical power. This will also allow us to accommodate a higher drop-out rate and those who are deemed ineligible after signing consent during physical examination screening without a modification.

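### The trial is sized at .01 for each of five outcomes, but the analysis paragraph tests three foot pairs per outcome without that level or an overall-test gate, and APSRA, named in H1.1 and H1.2, is in no model

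*Protocol*

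**What the plan says.** - **Level used for sample size** (Protocol 2.6, Power Analysis): the simulations use a type 1 "error of .01, as we have 5 outcomes of interest". That is .05/5. The NBWT scenario is described as "with 1 mean pair-wise difference in NBWT of 2 ft", and the mixed model is said to be the one in the methods text.
- **Analysis** (Protocol 2.6, Statistical Analysis): for H1.1 and H1.2 the listed outcomes are "Perceived Stability score, MOS, ABC, NBWT, or FSST (the dependent variables"), with prosthetic foot as fixed effect and participant as random effect. For all models, "pair-wise mean differences and 95% confidence intervals (CI) across the three feet will be estimated and tested for significance". No significance level is given there, and no condition for going on to the pairs.
- **Hypotheses** (Protocol 1.0, Specific Aim 1): both hypotheses name the same five measures plus a sixth. H1.1 ends with "less activity restriction (i.e., PROMIS Ability to Participate in Social Roles and Activities (APSRA)) after community use"; H1.2 ends with "less activity restriction (i.e., PROMIS APSRA) after community use".
- **Data collection** (Protocol 2.5, Visits 4, 5 and 6): the follow-up survey covers "satisfaction, balance, activity restrictions, fear of falling, and mobility while using the study assigned prosthetic foot". The construct behind APSRA is therefore collected with each study foot.

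**The concern.** The two paragraphs of section 2.6 are meant to describe one analysis, but they do not carry the same error rule. The sample size spends 5% as one test per outcome at .01. The analysis makes three comparisons per outcome and sets beside them an interval that corresponds to .05. An analyst who follows the analysis paragraph as written cannot tell which level decides a foot difference. No reading of it that leaves the pairs ungated gives the 5% that the sample size assumed.

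APSRA is a different problem. It is part of what Aim 1 claims, but no dependent variable in section 2.6 corresponds to it, including in the models for Aims 2 and 3. Followed as written, the plan reaches no conclusion on activity restriction.

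**Working it through.** **1. Inputs from the protocol.** Level .01 for five outcomes; three feet, so three pairs; NBWT within-participant SD 2.7 ft and difference 2 ft; MOS within-participant SD 1.0 cm and differences 1 cm and 0.7 cm; stated powers 81%, 91%, 98% and 87%. Assumptions: two-sided tests (sidedness is not stated), complete data, and one foot differing by d from two equal feet.

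**2. Reproducing the stated powers at .01.** Two candidate tests:
- Overall foot test, 2 df: noncentrality = n × Σ(μ − mean)² / SDw². With means (0, 0, d) the sum is (2/3)d².
- Single pair: SE = SDw × √(2/n), power ≈ Φ(d/SE − 2.576).

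For NBWT at n = 40: noncentrality = 40 × (2/3) × 4 / 7.29 = 14.63; SE = 2.7 × √(2/40) = 0.604, so d/SE = 3.31 and power ≈ Φ(0.74) = 77%.

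| Scenario | Stated | Overall test, F / chi-square | Single pair, t / normal |
|---|---|---|---|
| NBWT 2 ft, n = 40 | 81% | 79.6 / 82.6% | 74.7 / 76.9% |
| NBWT 2 ft, n = 50 | 91% | 90.0 / 91.7% | 85.7 / 87.0% |
| MOS 1 cm, n = 40 | 98% | 98.2 / 98.8% | 96.4 / 97.1% |
| MOS 0.7 cm, n = 50 | 87% | 85.5 / 87.5% | 80.6 / 82.2% |

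All four stated figures lie within 2 points of the overall test. Three of the four are not reproduced by a single pair-wise test. The sample size therefore appears to rest on one overall test per outcome, although the text words it as power for a pair-wise difference.

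**3. Error rate under each reading** (no true difference; five outcomes).
- Planned: 5 × .01 = .05, or 1 − 0.99⁵ = 4.9% if the outcomes are independent.
- Three correlated contrasts on one outcome, ungated (simulated): 2.7% at .01 and 12.2% at .05.
- Over five independent outcomes: 1 − (1 − .0271)⁵ = 12.8% at .01; 1 − (1 − .1219)⁵ = 47.8% at .05.
- With correlated outcomes (simulated):

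| Outcome correlation | Ungated pairs at .01 | Ungated pairs at .05 |
|---|---|---|
| 0 | about 13% | about 48% |
| 0.7 | about 9% | about 33% |

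- Pairs tested only after a significant overall test at .01: 1.0% per outcome, and 4.96% over five independent outcomes.

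**4. Outcome count.** H1.1 and H1.2 each name six: Perceived Stability, MOS, ABC, NBWT, FSST and APSRA. The analysis lists five and the power paragraph counts five, so those two agree, and .05/5 = .01 is correct for what is modelled. If APSRA were added at .01 with one test each, the total would be 6 × .01 = .06 (1 − 0.99⁶ = 5.9%). Holding 5% over six needs .05/6 = .0083.

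**The case against.** The strongest reply is that the protocol contains no .05 decision rule. A 95% interval is a usual reporting interval and is often printed beside a stricter test. The only type 1 error in the document is .01, and the stated powers fit an overall foot test at that level. If the pairs are read only after that test, the planned 5% holds. Gating and pair-wise adjustment are also often left to an SAP.

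Much of this stands. A reader might infer that the plan commits to a 33% to 48% false-positive rate; the text does not support that, because it states no level for the pair-wise tests. What remains is that the protocol itself ties the pair-wise differences to significance, gives 95% as the only level in that paragraph, and does not state the gate on which the 5% depends. Even with .01 carried over, ungated pairs give 9% to 13%. This is a mismatch between two paragraphs of one section, not merely detail left for later.

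Two further inferences should be resisted:
- A reader might say that the divisor of five is one short. It is not, while APSRA is outside the models; the fault is the missing analysis.
- A reader might double the error rate on the ground that low- and high-mobility groups wear different foot sets. The analysis paragraph does not say that the groups are analysed separately, so no such figure is supported.

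**Conclusion.** The point holds in two parts.

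1. **Error rule.** The planned 5% is secured only if the pairs are gated by an overall test at .01, and the analysis paragraph does not say so. The gap is about 9% to 13% against 5% if .01 is used ungated. It reaches about 33% to 48% only if the 95% intervals are taken as the decision rule.
2. **APSRA.** It is hypothesised twice, its construct is surveyed at follow-up, and it has no model.

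The error rates assume no true foot difference, a common correlation among outcomes between 0 and 0.7, and a family made up of the five outcomes of one hypothesis. H1.1 uses medial/lateral MOS and H1.2 anterior/posterior MOS, so treating Aim 1 as a single family would need a further choice. The match of the powers to the overall test assumes the (0, 0, d) pattern of means. Neither part changes the design or shows the recruitment target to be wrong.

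**What to change.** In protocol section 2.6:

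1. Add APSRA as a dependent variable for H1.1 and H1.2. Either label it secondary and keep .01 for the five, or make it a sixth outcome at .05/6 = .0083.
2. State the chosen level in the Statistical Analysis paragraph. Test the overall 2-df foot effect at that level first, and test the three pairs at the same level only if it is significant. For three feet this is a closed testing procedure and needs no further adjustment.
3. Base any claim of significance on that level or on the matching interval (99%, or 99.2% for .0083), and call the 95% intervals descriptive.
4. Say in the Power Analysis that the stated powers match the overall foot test. Add that pair-wise NBWT power at .01 is about 75% to 77% at n = 40 and 86% to 87% at n = 50.

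**Cost.** Wording, and wider intervals behind any claim. Keeping .01 leaves the stated powers as they are. Moving to .0083 takes 1 to 2 points: overall-test NBWT power goes from 80–83% to 78–81% at n = 40 and from 90–92% to 89–91% at n = 50. The gate also depends on the pattern of means. If the third foot lies midway between the other two instead of equalling one of them, simulated overall-test power for NBWT at .01 is about 63% to 66% at n = 40 and 77% to 79% at n = 50. The assumed pattern should therefore be stated.

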## 2.0 Study Procedures

### 2.1 Study Design

#### *Study Population*

Participants will be men and women, age 18 or over, with a unilateral TTA that have been fit with a prosthesis and use it on a regular basis (full inclusion/exclusion criteria are listed below). Participants will be recruited at two sites: VA Puget Sound and Minneapolis VA. We will conduct a participant-blinded cross-over study with repeated measurements. Data collection methods will be identical at both sites. Participants will walk in the laboratory with the PFE and with corresponding/matched, commercial prosthetic feet under various walking conditions (e.g. level ground, incline, cross slopes, uneven ground). Participants will then wear each of the commercial feet at home and in the community for one-week periods. Participants will then return to the laboratory for follow-up visits after each one-week trial period to assess foot preference, stiffness perception, balance confidence, activity restrictions, stability, and falls-related outcomes in order to determine whether the PFE and/or a brief trial of commercial feet in the laboratory are able to predict mobility, stability, and falls-related outcomes after one week of use in the home and community setting.

No exclusions based on sex, race, or ethnic status will be applied.

| Study Groups and sites (enrollment)               |                  |
|----------------------------------------------------------|------------------|
| Seattle VA: Participants with transtibial amputation     | up to 50         |
| Minneapolis VA: Participants with transtibial amputation | up to 50         |
| Total VA sites                                    | up to 100 |

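### The power labelled as that of a pair-wise difference is 4 to 6 points above a two-sided pair-wise test for three of four figures, and the recruitment target of 60 is not reconciled with enrolment of up to 100.

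*Protocol*

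**What the plan says.** Section 2.6 (Statistical Analysis) fits linear mixed models with prosthetic foot as the fixed effect and participant as a random effect, and then states that "pair-wise mean differences and 95% confidence intervals (CI) across the three feet will be estimated and tested for significance".

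The Power Analysis paragraph of the same section simulates 5000 datasets per scenario. The simulated analysis is described only by reference: "linear mixed effects regression was carried out as described in the methods section". The significance level is a type 1 "error of .01, as we have 5 outcomes of interest". For NBWT, the pilot data are quoted "with between and within participant standard deviation (SD) 4.1 and 2.7, respectively", and the simulation assumes one pair-wise mean difference of 2 ft. The NBWT result reads "We estimate 81% and 91% power to detect differences in NBWT of 2 ft. for sample sizes of 40 and 50 respectively". The MOS result, with between- and within-participant SDs of 1.9 and 1.0 cm, reads "We estimate 98% power to estimate a pair-wise difference between prosthetic feet of 1 cm for 40 participants", followed by 87% for 0.7 cm with 50 participants.

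On numbers, the paragraph says "we will recruit 60 participants (30 at each site), so that even if 20% of the recruited participants drop out" power remains adequate. It adds that the 60 also leaves room for higher drop-out and for people found ineligible after consent. The enrolment table in section 2.1 (Study Population) has a row "Minneapolis VA: Participants with transtibial amputation | up to 50", the same ceiling for Seattle, and a total of up to 100.

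**The concern.** The planned analysis is pair-wise and reports 95% intervals, which are naturally two-sided. The power paragraph also describes its effects as pair-wise differences. A reader will therefore take 81%, 91%, 98% and 87% as the power of a two-sided pair-wise contrast at .01. If they belong to another test, the trial's justification overstates what the reported contrasts can detect. NBWT at n = 40 matters most, because there the choice of test decides whether power is above or below 80%.

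The second matter is the planned size. Two sections give different recruitment numbers, and nothing says which one ends recruitment.

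**Working it through.** **Inputs (protocol section 2.6).** Within-participant SD s = 2.7 ft (NBWT) and 1.0 cm (MOS); differences d = 2 ft, 1 cm and 0.7 cm; n = 40 and 50; three feet per participant; type 1 error .01. Sidedness, the test counted and the full set of three means are not given. With complete data, the between-participant SD cancels from within-participant contrasts.

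**Step 1. Two-sided pair-wise test at .01.** SE = s × √(2/n). Normal approximation: power = Φ(d/SE − 2.576). The t version uses the noncentral t with 2(n − 1) degrees of freedom.

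- NBWT, n = 40: SE = 2.7 × √(2/40) = 0.604; d/SE = 3.313; Φ(0.737) = 76.9%; t version 74.7%.
- NBWT, n = 50: SE = 0.540; d/SE = 3.704; Φ(1.128) = 87.0%; t version 85.7%.
- MOS 1 cm, n = 40: SE = 0.224; d/SE = 4.472; Φ(1.896) = 97.1%; t version 96.4%.
- MOS 0.7 cm, n = 50: SE = 0.200; d/SE = 3.500; Φ(0.924) = 82.2%; t version 80.6%.

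**Step 2. Which tests reproduce the stated figures.** For the overall 2-df foot test with means (0, 0, d), the noncentrality is (2/3) × n × d²/s², which is 14.63, 18.29, 26.67 and 16.33 for the four cases. This is referred to F with 2 and 2(n − 1) degrees of freedom, or to chi-square with 2. The one-sided .01 pair-wise test uses the SEs of step 1 and the t distribution.

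| Case | Stated | Pair-wise two-sided .01 (t to normal) | Overall 2-df test (F to chi-square) | Pair-wise one-sided .01 (t) |
|---|---|---|---|---|
| NBWT 2 ft, n = 40 | 81% | 74.7–76.9% | 79.6–82.6% | 82.3% |
| NBWT 2 ft, n = 50 | 91% | 85.7–87.0% | 90.0–91.6% | 90.8% |
| MOS 1 cm, n = 40 | 98% | 96.4–97.1% | 98.2–98.8% | 98.1% |
| MOS 0.7 cm, n = 50 | 87% | 80.6–82.2% | 85.5–87.5% | 87.0% |

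Both right-hand columns come within 2 points of all four stated values. The two-sided pair-wise column does so only for the 98%.

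**Step 3. Size of the gap.** Stated minus two-sided pair-wise: 4.1–6.3, 4.0–5.3, 0.9–1.6 and 4.8–6.4 points. Simulation noise does not explain the three larger gaps: with 5000 datasets the standard error at 81% is √(0.81 × 0.19/5000) = 0.55 points.

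**Step 4. After drop-out.** 60 × 0.8 = 48. At n = 48 the two-sided pair-wise power (t to normal) is:

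- NBWT 2 ft: SE = 0.551, 83.9–85.4%.
- MOS 0.7 cm: SE = 0.204, 78.6–80.3%.

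**Step 5. Planned number.** Section 2.6: 30 + 30 = 60. Section 2.1: 50 + 50 = 100. Section 2.6 says the 60 already covers ineligibility after consent and extra drop-out, so screen failures do not account for the difference of 40.

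**The case against.** The strongest reply is that nothing shows the stated figures to be wrong. Sidedness is not given, H1.1 and H1.2 are directional, and a one-sided .01 pair-wise t test reproduces the figures about as well as the overall test does. The NBWT sentence speaks only of detecting differences, and the simulated model has foot as its fixed effect, so an overall test is also consistent with it. This stands. The documents do not show that the overall test is the only explanation, or that the simulation was faulty. It does not remove the problem, because neither explanation is written down and the planned 95% intervals point to a two-sided contrast.

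The gaps are also modest, and the 98% figure, the one most plainly labelled pair-wise, is barely affected. That stands too.

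Two stronger readings should be resisted:

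- A reader might infer that 48 completers contradicts the n = 50 scenarios. The protocol never promises 50. It gives 40 and 50 as scenarios, and 48 lies between them. It also calls 20% conservative against a rate below 5% in the current emulator study. All that follows is that the 91% and 87% are not secured if 20% do drop out.
- A reader might take the phrase about one pair-wise difference literally and assume equally spaced means (0, d/2, d). The overall test would then have only 63–67%, 77–79%, 93–94% and 71–73%. The protocol does not give the three means, and this pattern does not reproduce its figures, so it is evidently not what was simulated.

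On enrolment, "up to" marks a ceiling, so 100 and 60 are not strictly contradictory. They are nonetheless unreconciled, for the reason in step 5.

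**Conclusion.** The point holds as one of labelling and moderate overstatement. If the target is a two-sided pair-wise contrast at .01, three of the four stated powers are about 4 to 6 points too high, and NBWT at n = 40 falls from 81% to about 75–77%, below 80%. The fourth agrees within 2 points. If the figures belong to the overall foot test with one foot differing from both others, or to a one-sided pair-wise test, they are sound as numbers but not identified as such.

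This rests on the protocol's SDs, complete data on all three feet, a common within-participant SD and two-sided testing. The last is an assumption drawn from the planned 95% intervals. The unreconciled 60 and up to 100 stand independently of these assumptions. No change of design follows from either part.

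**What to change.** In the Power Analysis paragraph of section 2.6, name the test whose power was simulated (overall foot test or a single contrast), its sidedness and the three assumed means, and label the four figures accordingly. If two-sided pair-wise contrasts are the target, replace the figures with about 75–77%, 86–87%, 96–97% and 81–82%, and add the values at 48 completers: about 84–85% for NBWT 2 ft and 79–80% for MOS 0.7 cm.

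In sections 2.1 and 2.6, state one planned number at which recruitment stops, and say what the ceiling of 100 is for if it is kept. The sponsor must supply that explanation, because the protocol does not contain one.

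The cost is rewording two places. Under the two-sided reading, the stated power also becomes somewhat less favourable.
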